## Safety endpoints

- Number of Adverse events and serious adverse events will be monitored during the course of the study.
- Changes in liver, renal, coagulation will be monitored during the course of the study.

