### Randomisation and Allocation Concealment Protocol

Randomisation will be conducted external to the primary research team (investigators listed at the start of this document) by a research officer of the National Institute of Complementary Medicine (NICM). This person will be responsible for producing computer generated randomisation treatment sequences which randomly associate a randomisation number with either active or placebo treatment. NICM's Clinical Trials Manager and Strategic Operations Manager are responsible for securely storing the randomisation allocation in a restricted access electronic file.

Randomisation numbers will be allocated in permuted blocks of 6 randomisation numbers starting from 001 to 238 with each block containing 3 active and 3 placebo assigned randomisation numbers. Sites will allocate the randomisation numbers in order of number sequence starting with the lowest number in each block and using all numbers in a block of 6 before starting with the next block of numbers. As soon as the randomisation number is assigned, it will be recorded on the screening log, in the participant source data file and electronic Case

Report Form (eCRF). Details of any participants randomised out of sequence will be notified immediately to the Coordinating chief investigator.

Investigators and/or pharmacists may request to break the blind for a participant if there is a clinical need to know the treatment allocation for a subject e.g. to manage the treatment of a serious adverse event. The site's Principal Investigator needs to discuss the reasons for breaking the blind with the Coordinating Investigator (or if unavailable, the Trial Coordinator). If this request is approved, it will be forwarded to the NICM Clinical Trials Manager. The NICM Senior Manager and Clinical Trials Manager will liaise with the Chief Investigator to process the code break request. When a participant allocation blinding is revealed, the participant ID, date, reason for opening, name of person and signature of who broke the seal, should be provided in writing. The Principal Investigator, Chief Investigator and Statistician will be notified of this information. The participants, principal investigators, research team members, trial medical practitioners, data collection nurses and other staff of the trial centres will have no knowledge of the randomisation assignments until follow-up outcome measures and data analysis are complete.

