### **Clinical Laboratory Parameters and Abnormal Laboratory Test Results**

For participants recruited in the Australian centres, tests will be performed by a certified pathology laboratory. Hard copies of all results will be provided to the investigator and transferred electronically to the clinical database.

The following laboratory tests will be performed at Screening, Week 4, Week 13, Week 26, Week 39, Week 52/EOT and Week 65:

|                     |                                                                         |
|---------------------|-------------------------------------------------------------------------|
| Haematology         | Haemoglobin (Hb)                                                        |
|                     | Haematocrit (Hct)                                                       |
|                     | Red Blood Cell Count (RBC)                                              |
|                     | Platelets Count (Plt)                                                   |
|                     | White Blood Cell Count (including a five part differential in absolute) |
| Coagulation testing | Prothrombin time (PT)                                                   |
|                     | Activated Partial Thromboplastin Time (APTT)                            |
|                     | Fibrinogen (FIB) Level                                                  |
| Liver Function      | Total Bilirubin (TBil)                                                  |
|                     | SGOT (AST)                                                              |
|                     | SGPT (ALT)                                                              |
|                     | Alkaline Phosphatase (ALP)                                              |
|                     | Albumin (ALB)                                                           |
|                     | Total Protein (TP)                                                      |

|                |                           |
|----------------|---------------------------|
| Renal Function | Blood urea nitrogen (BUN) |
|                | Creatinine (Cr)           |
| Electrolytes   | Sodium (Na)               |
|                | Potassium (K)             |
|                | Chloride (Cl)             |

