### **Study Procedures: Schedule of Assessments**

In response to the COVID-19 outbreak in Australia, study procedures have been amended to protect the safety and wellbeing of participants, their caregivers as well as the research team, and to minimise the impact of the outbreak on the SLT001 trial. Recruitment is to be paused until the trial centre's public health directive and the relevant governance body allow for recruitment to resume. All COVID-19-related strategies are detailed in Appendix 4 of this document. Once the COVID-19 outbreak ceases as per the Australian government's directive, Appendix 4 will cease to be used.

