### Safety Measures

- *Liver and renal function, and routine haematological and coagulation (PT, APPT and fibrinogen) tests* will be conducted at baseline, 4, 13, 26, 39 and 52 weeks after the commencement of the treatment.
- All adverse events will be recorded at each visit, including those suspected to be related to the treatment (such as headache, dizziness, vomiting, allergy, etc) and any worsening of symptoms will be closely monitored. An assessment of the relationship between the adverse events or abnormal test results and the treatment will be made by the chief investigators and

trial physicians. An adverse event will be followed up until it resolves or for up to a month after the study is concluded. Serious adverse events (SAEs) will be immediately reported to the Human Research Ethics Committee granting approval and Suspected Unexpected Serious Adverse Reactions (SUSARs) to the TGA, in accordance with their guidelines. The causality of SAEs will be thoroughly investigated.

| Week                                                     | -2 to 0          | 0                                | 2  | 4  | 13 | 26 | 39 | 52            | 65               |
|----------------------------------------------------------|------------------|----------------------------------|----|----|----|----|----|---------------|------------------|
|                                                          | Screening | Baseline                  |    |    |    |    |    | End Tx | Follow up |
| Window                                                   |                  | 0                                | ±3 | ±7 | ±7 | ±7 | ±7 | ±7            | ±7               |
| Initial neurological assessment                          | X                |                                  |    |    |    |    |    |               |                  |
| Medical History                                          | X                |                                  |    |    |    |    |    |               |                  |
| Vital signs (HR, BP, Ht, Wt)                             | X                |                                  |    | X  | X  | X  | X  | X             |                  |
| Physical Exam                                            | X                |                                  |    |    |    |    |    |               |                  |

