### **Missing data and protocol violations**

In the case of death, all measurements prior to death will be included in the analysis but all after death will be set to missing. To address withdrawals, loss to follow-up or non-compliance with the study analyses will be conducted on both an intention to treat (ITT) and per protocol (PP) basis. Withdrawing and non-compliant participants shall be encouraged to continue with data collection even if stopping treatment. Where data items are missing the last value carried forward method to replace missing data in the ITT analysis will be used. Participants who have significant deviations from the protocol will be removed from the PP analysis after the completion of the ITT analysis. Such significant deviations from the protocol will be determined and documented by the study clinician during the course of the study. Any deviation from randomisation, missing data and withdrawals will be fully reported for this purpose.

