|     | 2.5.2 Safety Pathology Testing at Week 39        | Conducted at hospital/local pathology laboratories | To further minimise risk, the Week 39 pathology test can be skipped if there are no abnormal and unresolved findings at Week 26. Otherwise follow 2.5.1 for pathology testing.                                                                                                                                                                                                                                                                                                                                                                                                                                                                                                                                                 | All Centres    | If abnormalities are recorded in the previous tests, Week 39 pathology test will be conducted as per Item 2.5.1                                                                                                                                                                                                                         |

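### While Appendix 4 is active, Week 39 safety bloods may be omitted on the basis of the participant's own Week 26 result, and the stated carry-forward rule would fill the gap with a clean value

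*Protocol*

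**What the plan says.** The laboratory safety endpoint in Protocol section 1.3 is general: "Changes in liver, renal, coagulation will be monitored during the course of the study". Outside the contingency plan, Week 39 bloods are scheduled for everyone. Section 3.3 (Clinical Laboratory Parameters) states "The following laboratory tests will be performed at Screening, Week 4, Week 13, Week 26, Week 39, Week 52/EOT and Week 65". Section 5.1 (Safety Measures) says that the tests "will be conducted at baseline, 4, 13, 26, 39 and 52 weeks after the commencement of the treatment". The Week 39 Visit list and Table 1 agree on Week 39.

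Appendix 4, item 2.5.2 changes this for the pandemic period: "the Week 39 pathology test can be skipped if there are no abnormal and unresolved findings at Week 26". The Note/Action column of the same row gives another trigger: "If abnormalities are recorded in the previous tests, Week 39 pathology test will be conducted as per Item 2.5.1". Section 3.3 (Schedule of Assessments) makes the arrangement temporary, since once the outbreak ends "Appendix 4 will cease to be used".

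On missing values, section 5.2 states "Where data items are missing the last value carried forward method to replace missing data in the ITT analysis will be used". Nothing there excludes laboratory values or tests omitted under Appendix 4. Appendix 4, item 2.1 applies the same carry-forward approach to vital signs.

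**The concern.** Under item 2.5.2 a participant with an abnormal and unresolved Week 26 finding is tested at Week 39, and one without may not be. The Week 26 result is post-randomisation and treatment may affect it, so the arms can be tested at different rates and for reasons tied to the outcome.

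Two simple ways of filling a Week 39 by-arm table then go wrong. Carry-forward gives the skipped participants the very result that qualified them to be skipped, so new onset by Week 39 cannot appear among them. An observed-case table leaves them out and is weighted towards participants who already had abnormalities.

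Liver, renal and coagulation changes are the protocol's named laboratory safety endpoints, and section 4.2 lists impaired liver and kidney function among the possible moderate to major adverse events. For a skipped participant the nominal gap between blood tests doubles from 13 weeks (26 to 39) to 26 weeks (26 to 52). With the ±28-day windows of Appendix 4, item 5.2 it can reach (52 + 4) − (26 − 4) = 34 weeks.

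**Working it through.** The protocol states no figure on this point, so there is nothing to reproduce. It gives no laboratory abnormality rates, no share of Week 39 visits falling under Appendix 4, and no share of eligible participants who skip. All rates below are assumptions. They show direction and range and are not estimates for this trial.

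Inputs taken from the protocol: the Week 26 trigger in item 2.5.2, the carry-forward rule in section 5.2, and 1:1 allocation, with "each block containing 3 active and 3 placebo assigned randomisation numbers". Randomisation protects a comparison of everyone at Week 39. It does not protect a comparison of those tested because of a Week 26 result.

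Notation, per arm: p = probability of an abnormal, unresolved finding at Week 26; q = probability that it is still abnormal at Week 39; o = probability that a participant clean at Week 26 is abnormal at Week 39; s = share of clean participants who skip.

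- True Week 39 rate = pq + (1 − p)o
- Carry-forward rate = pq + (1 − p)(1 − s)o
- Observed-case rate = [pq + (1 − p)(1 − s)o] / [p + (1 − p)(1 − s)]

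**Scenario A, arms truly differ.** Placebo p = 5%, q = 60%, o = 3%; SLT p = 10%, q = 60%, o = 8%.

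- True placebo rate: 0.05 × 0.6 + 0.95 × 0.03 = 5.85%
- True SLT rate: 0.10 × 0.6 + 0.90 × 0.08 = 13.2%
- True difference: 7.35 points

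**Scenario B, no true difference at Week 39.** Placebo p = 10%, q = 30%, o = 5%; SLT p = 5%, q = 90%, o = 3.16%.

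- True placebo rate: 0.03 + 0.045 = 7.5%
- True SLT rate: 0.045 + 0.03 = 7.5%

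**Scenario C, identical arms.** Both p = 5%, q = 60%, o = 3%; true rate 5.85% in each.

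SLT minus placebo, in percentage points:

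| Skip uptake s | A: observed cases | A: carry-forward | B: observed cases | B: carry-forward | C: either method |
|---|---|---|---|---|---|
| 0% | 7.4 | 7.4 | 0 | 0 | 0 |
| 25% | 8.0 | 6.3 | 0.6 | 0.4 | 0 |
| 50% | 9.0 | 5.2 | 1.9 | 0.8 | 0 |
| 75% | 11.1 | 4.1 | 5.6 | 1.1 | 0 |
| 100% | 0.0 | 3.0 | 60 | 1.5 | 0 |

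Worked cell, scenario A at s = 50%. The carry-forward rates are 0.06 + 0.9 × 0.5 × 0.08 = 9.6% on SLT and 0.03 + 0.95 × 0.5 × 0.03 = 4.425% on placebo, a difference of 5.2 points. The observed-case rates are 0.096/0.55 = 17.5% and 0.04425/0.525 = 8.4%, a difference of 9.0 points.

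In scenario A at full uptake, carry-forward misses 0.072/0.132 = 55% of the true Week 39 abnormalities on SLT and 0.0285/0.0585 = 49% on placebo. In scenario C the arms stay equal, but the rate in each arm is still wrong: at full uptake it is 60% in observed cases and 3.0% under carry-forward, against a true 5.85%.

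The scale of measurement also matters. Take p = 15% on SLT and 5% on placebo, with q = 60% and o = 3% in both. The true rates are 11.55% and 5.85% (5.7 points, ratio 1.97). Carry-forward at full uptake gives 9% and 3% (6.0 points, ratio 3.0). The difference barely moves and the ratio rises by half.

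**The two triggers.** These calculations use the Week 26 trigger. The Note/Action wording is limited neither to Week 26 nor to unresolved findings. A participant whose Week 13 abnormality had resolved by Week 26 may be skipped under one column and must be tested under the other. Under the wider trigger more participants are tested and the figures change, but testing still depends on earlier results.

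**The case against.** The strongest reply is that the protocol plans no Week 39 comparison. The endpoint is change over the study, section 5.2 only tallies adverse events by group, and by-visit laboratory tables are ordinary SAP material. Appendix 4 is also a declared and temporary override of the schedule, so its departure from section 5.1 and Table 1 is not a contradiction. Both points stand. What remains is a rule that the protocol does state, carry-forward, which gives a wrong Week 39 value when applied to a test omitted because its predecessor was clean.

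A second reply is that missingness driven by an observed Week 26 value can be handled by a likelihood model that includes that value. This is true where some clean participants are still tested. If all of them skip, the model extrapolates. In either case the missing-data method that the protocol states is carry-forward.

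A reader might infer more than the text supports:

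- **That Week 39 laboratory data exist only for a selected group.** Skipping is optional and confined to the pandemic period, so clean participants who were tested also contribute.
- **That the protocol leaves skipped participants unscored.** Section 5.2 has a general rule, and that rule is the difficulty.
- **That a real difference between arms would vanish.** In scenario A this happens only in observed cases at 100% uptake, and only because persistence was set equal in both arms. At 25% to 75% uptake the observed-case difference is too large, not too small.
- **That most participants would take this path.** The protocol gives no uptake.

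**Conclusion.** The point holds in limited form. For visits under Appendix 4, Week 39 laboratory data can be missing in a result-dependent way. Carry-forward then hides abnormalities that begin between Weeks 26 and 39, unless they persist to Week 52 and are picked up there. Observed-case summaries over-represent participants with earlier abnormalities.

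Bias between arms requires the arms to differ in Week 26 status, persistence or new onset, and it can go in either direction. Its size is unknown. The scenarios rest on assumed rates and uptake and on the Week 26 trigger.

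Weeks 4, 13, 26 and 52 have no such skip option and can support the between-arm laboratory conclusions. They are not wholly free of the problem: under items 2.5.1 and 3.5, when a participant declines both ways of giving blood, earlier pathology results help decide whether that participant continues.

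Separately, the two triggers in item 2.5.2 do not match, and centres could apply them differently.

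**What to change.** 1. Flag in the eCRF each Week 39 laboratory test skipped or done under item 2.5.2.
2. State in section 5.2 that Week 39 laboratory values skipped under that item are neither carried forward nor counted as normal.
3. Base between-arm laboratory conclusions on Weeks 4, 13, 26 and 52. Report Week 39 descriptively, with numbers tested and skipped by arm, and keep every observed abnormal result visible in the tables.
4. Reconcile the Alternate Arrangements and Note/Action triggers in item 2.5.2. Which one should apply is for the investigators and sponsor to decide, and nothing here favours either.

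The cost is a short addition to section 5.2, one eCRF flag and a wording correction in Appendix 4. The downside is a smaller, descriptive-only Week 39 laboratory table for the pandemic period.

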### 3. SLT001 Trial Contingency Measures for Weeks 0, 26 and 52 Visits

| .   | Activity                                     | Pre-COVID Status               | Alternate Arrangements                                                                                                                                                                                                                                                                                                                                                                                                                                                                                                                                                                                               | Responsibility | Note/Action                                                                                                                                                                                                                                                                                                                                                                                                                                                                                                                                               |
|-----|----------------------------------------------|--------------------------------|----------------------------------------------------------------------------------------------------------------------------------------------------------------------------------------------------------------------------------------------------------------------------------------------------------------------------------------------------------------------------------------------------------------------------------------------------------------------------------------------------------------------------------------------------------------------------------------------------------------------|----------------|-----------------------------------------------------------------------------------------------------------------------------------------------------------------------------------------------------------------------------------------------------------------------------------------------------------------------------------------------------------------------------------------------------------------------------------------------------------------------------------------------------------------------------------------------------------|
| 3.0 | Week 0, 26 and 52 visits (assessment visits) | Face-to-face on-site           | 
Part of the testing including VaDAS-cog, Exit-25, CLOX, CIBIS/CIBIC plus will be conducted as per Item 3.1.
 
Part of the testing including ADCS-ADL, DEMQOL, DEMQOL-Carer and NPI can be conducted remotely (i.e., over the phone) to reduce face-to-face contact time as per Item 3.2
                                                                                                                                                                                                                                                                                                                  | All Centres    | 
Centres will need to assess their current policies and procedures to determine appropriate action for these visits.
 
Researchers to obtain verbal consent to collect any data remotely and record this in the source visit notes.
                                                                                                                                                                                                                                                                                                            |
| 3.1 | VaDAS-cog, Exit-25, CLOX, CIBIS/CIBI C plus  | Conducted face-to-face on site | 
The options include:
 
 
1) Verbally consenting to continuing to visit the trial centre for these assessments at the site where such visits are still permitted; COVID-19 safety check and protection measures must be taken as per Item 3.4
 
2) Verbally consenting to being assessed at a nominated community centre; COVID-19 safety check and protection measures must be taken as per Item 3.4
 
3) Verbally consenting to receive a home visit from assessors; COVID-19 safety check and protection measures must be taken as per Item 3.4
 
 | All centres    | 
For Options 1 & 2, Sponsor to cover the costs of taxi/Uber if needed to avoid public transport.
 
For face-to-face visits: the assessors, participant and caregiver will thoroughly wash their hands and/or use hand sanitizer prior to and following a face-to-face visit. Masks and/or gloves to be used in line with local health advice. Centres will need to ensure PPE supplies are readily accessible if conducting face-to-face visits.
 
If unable to collect data, record as Not Done and explain why in the source notes.
 |

|     |                                         |                                                            |                                                                                                                                                                                                                                                                                                                                                                                                         |                |                                                                                                                                                                                                                                                                            |
|-----|-----------------------------------------|------------------------------------------------------------|---------------------------------------------------------------------------------------------------------------------------------------------------------------------------------------------------------------------------------------------------------------------------------------------------------------------------------------------------------------------------------------------------------|----------------|----------------------------------------------------------------------------------------------------------------------------------------------------------------------------------------------------------------------------------------------------------------------------|
|     |                                         |                                                            | 4) For the sites where both on site and home visits are not feasible, and/or participants are unwilling to attend in person, the possibility of using telehealth or videoconferencing to conduct these assessments will be explored; this option is not viable for the baseline visit (Week 0)                                                                                                          |                |                                                                                                                                                                                                                                                                            |
| .   | Activity                                | Pre-COVID Status                                           | Alternate Arrangements                                                                                                                                                                                                                                                                                                                                                                                  | Responsibility | Note/Action                                                                                                                                                                                                                                                                |
| 3.2 | ADCS-ADL, DEMQOL, DEMQOL-carer, and NPI | Conducted face-to-face on site                             | These tests may be conducted remotely via phone to reduce face-to-face assessment time of Item 3.1, Options 1, 2, and 3.                                                                                                                                                                                                                                                                                | All Centres    | Researchers to obtain verbal consent to collect any data over the phone and record this in the source visit notes.                                                                                                                                                         |
| 3.3 | IP dispensing (Week 26 only)            | Dispensed on site by the hospital pharmacy or investigator | 
Two available options:
 
(1) Centres where no on-site visits are possible: 6-month supply of IP to be delivered by a courier service or through a home visit by a study team member, with visit 6 and 7 diaries, and instructions to keep empty packaging/leftover capsules
 
(2) Centres where site visits are still allowed: IP to be collected from pharmacy or delegated personnel
 | All Centres    | 
Obtain verbal consent to receive 6-month IP supply and record this in source notes.
 
Centres will organise delivery of IP.
 
Compliance check: Participants will be asked to keep boxes and return them together with unfinished capsules at next visit.
 |

|     | Activity                 | Pre-COVID Status                                   | Alternate Arrangements                                                                                                                                                                                                                                                                                                                                                                                                                                                                                                                                                                                                                                                                                                                   | Responsibility      | Note/Action                                                                                                                                                                                                                                                                                                                                                    |
|-----|--------------------------|----------------------------------------------------|------------------------------------------------------------------------------------------------------------------------------------------------------------------------------------------------------------------------------------------------------------------------------------------------------------------------------------------------------------------------------------------------------------------------------------------------------------------------------------------------------------------------------------------------------------------------------------------------------------------------------------------------------------------------------------------------------------------------------------------|---------------------|----------------------------------------------------------------------------------------------------------------------------------------------------------------------------------------------------------------------------------------------------------------------------------------------------------------------------------------------------------------|
| 3.4 | COVID-19 safety check    | Not applicable                                     | 
(1) Screen all participants over the phone for cold and flu symptoms, recent overseas or interstate travel and any close contact with a confirmed or suspected COVID-19 case in the past 14-days
 
 
Participants with these symptoms should be referred to qualified facilities for further investigation
 
Participants with these symptoms requesting advice should be directed to the Health Direct Line [name] or website https://www.healthdirect.gov.au/coronavirus
 
 
(2) If the participant is diagnosed with a coronavirus infection, trial medication may be suspended until symptoms resolve
 | All Centres         | 
(1) Personnel to conduct COVID-19 safety check with every call to a participant and delegated Investigators must review any reports of symptoms;
 
(2) Do not see or assess participant on study instruments, or proceed with pathology test, if symptoms present and cause is being investigated. Delay appointment until they have been cleared.
 |
| 3.5 | Safety Pathology Testing | Conducted at hospital/local pathology laboratories | 
If participant passes the COVID-19 checks, participant will be offered to verbally consent to the following two options:
 
(1) Continue to use the current pathology lab for the testing when on-site visit to pathology lab is permitted
 
(2) Home visit of a study team member or a mobile venipuncturist to take blood and deliver to the pathology lab for analysis; infection control procedures will be enacted as per Item 3.1
 
If the participant declines to take either option, the medical history and previous pathology results of the participant will be assessed by the PI and coordinating CI to determine if this participant can continue in the trial
                                        | All Centres
NICM | 
For Option 1, Pathology slip will be provided to participant; Sponsor to cover the costs of taxi/Uber if needed to avoid public transport.
 
For Option 2, Sponsor to cover the mobile blood collection services if relevant.
 
Centres to record verbal consent to remote blood collection in source visit notes.
                            |

